### Withdrawals

A patient can be withdrawn from the study if:

Consent/agreement is withdrawnThe participant loses capacityIt is found that they were recruited in errorThey have omitted more than one consecutive scheduled fortnightly assessment by the researcher, or omitted a total of three or more of these visits during the 24 week study, or before healing is confirmedThe participant is lost to follow-up

### Assessment of safety

#### Adverse device effect (ADE)

This refers to any untoward and unintended response to a medical device, including any effect resulting from insufficiencies or inadequacies in the instructions for use or the deployment of the device and any effect that is a result of a user error. ADEs will be recorded as they are reported whether spontaneously volunteered or in response to questioning about well-being at trial visits. All ADEs will be documented in the subject’s medical records and CRF and will be followed until resolution, or for at least 30 days after discontinuation of the use of the device, whichever comes first. The investigator will assess causal relationship of the ADE to the investigational device according to the following classification:

None: no relationship with investigational device. Other factor(s) certainly or probably causativePossible: reasonable possibility that the event was caused by the device, even though other possible causative factor(s) may existProbable: the event was certainly or probably caused by the device, even though other possible causative factor(s) may exist

The following definitions for rating severity of ADEs may be used:

Mild: signs or symptoms which are easily tolerated and are transient and only mildly irritating. There is no loss of time from normal activities and symptoms do not require medication or a medical evaluationModerate: discomfort sufficient to cause interference with usual activities or require therapeutic intervention; for example, concomitant medicationSevere: incapacity with inability to do work or undertake usual activities

#### Foreseeable ADEs

Foreseeable ADEs are those related to worsening of the clinical state of the ulcer and will be reported as secondary outcomes. These include

*Ulcer-related outcomes*

Increase in ulcer area

Infection

Major and minor amputation

Ulcer recurrence

Secondary ulceration on either limb

*Patient-related outcomes*

Increase in pain

Worsening mood or function

Hospital admission (relating primarily to the heel ulcer)

Death from pre-existing medical conditions

SADEs

An ADE that has resulted in any of the consequences characteristic of the serious criteria or that might have led to any of these consequences if suitable action had not been taken or if circumstances had been less opportune. These serious criteria are:

DeathLife threatening illness or injuryHospitalisation or prolongation of hospitalisationPermanent impairment of body structure or body functionMedical or surgical intervention required to prevent any of the above

An unexpected SADE refers to any SADE, the specificity or severity of which is not consistent with the current protocol.

*SADE Reporting*

All SADEss must be reported immediately to the Sponsor and will be documented in the subject’s medical records and CRF. All SADEs must be followed until resolution, or for at least 30 days after discontinuation of device use, whichever comes first.

### Statistical analysis

Appropriate descriptive statistics will be presented for each variable. Two-sided statistical test will be performed and presented with exact *P*-values, with interval estimates constructed using 95% as the level of confidence.

Descriptive statistics, analytical methods and sample size considerations will be included. The study team together with the investigators will make the decisions regarding individual values belonging to a patient to be excluded from the analysis; for example, out of range values/values that cannot be objectively verified. The investigators will make the final decision regarding coding on the reason(s) for withdrawal. The safety population (SP) will comprise all randomised patients for the study

The intention-to-treat (ITT) population is defined as all subjects who were randomised. Given the study is based on a population with an expected high morbidity, the attrition rate will be monitored closely. If the missing primary outcome data fall within the 20 to 25% level, then ITT will be completed without imputation in the first instance and repeated with multiple imputation as a sensitivity analysis. ITT is equal to SP in this study. Once a participant has a healed wound, which is confirmed as ‘healed’, they will no longer participate in the intervention phase of the study, as they will have achieved the primary outcome. Such participants will be deemed to have completed their participation in the efficacy part of the study and their data will be included in the numbers ‘healed’ by 24 weeks.

Per protocol (PP) population is defined as a subset of ITT population that has completed the treatment period of maximum 24 weeks according to the protocol. The following will be regarded as a protocol violation necessitating exclusion from the PP analysis:

Failure to use the study intervention (fibreglass heel cast) as recommended for more than 7 consecutive days, or for more than a cumulative total of 14 days during the course of the 24-week studyOmission of more than one consecutive scheduled fortnightly assessment by the researcher, or omission of a total of 3 or more of these visits during the 24-week study

Statistical analyses of relevant safety and all efficacy variables will be performed on the ITT population. Additionally, statistical analyses of efficacy variables concerning ulcer measurements will be performed on the PP population. If ITT and PP analyses of efficacy produce similar results, only the ITT analysis will be presented in the report, and the PP analysis will briefly be summarised.

### Statistical methods

All assumed continuously distributed variables will be investigated with regards to distribution. Transformation to unconstrained scales for ulcer area and VAS for pain will be considered. All continuously distributed variables will be summarised by treatment at measured time points with n = number of subjects, mean, 95% confidence interval (CI) of mean, median, standard deviation (SD), minimum, and maximum. Change from the baseline to the end will also be summarised by treatment with n = number of subjects, mean, median, SD, 95% CI of mean, minimum and maximum. All categorical (discrete including ordinal) variables will be presented in contingency tables showing counts and percentages for each treatment group at all time points.

#### Demographic and other baseline variables

All demographic and diagnostic ulcer assessments at baseline will be presented descriptively with counts and rates. In addition, age will be given descriptively with n, mean, median, SD, minimum-maximum. These data will be presented by trial arm at baseline.

#### Primary outcome

Healing will be defined as epithelialisation maintained for 4 weeks and will be confirmed by an observer blind to randomisation group. Outcomes for all patients randomised will be presented using a CONSORT flow diagram.

*Classification of outcome will include the following rule set:*Amputation of the target limb is a ‘failed’ outcome and classified as ‘not-healed’For those who achieve healing during the intervention phase (and are confirmed as healed) but have an active ulcer at the 24-week assessment will be counted as ‘healed’ but the recurrence/new ulcer will be noted as a secondary outcomeFor those who achieve healing during the intervention phase (and are confirmed as healed) but do not attend for the 24-week assessment will be counted as ‘healed’If the missing primary outcome data fall within the 20 to 25% level, then ITT will be completed without imputation in the first instance and repeated with multiple imputation as a sensitivity analysis

The primary endpoint will be percentage of all ulcers healed at or before 24 weeks (6 months). Based on the binary nature of the outcome, the unadjusted analysis of the effect of treatment on the primary outcome will be assessed using Logistic Regression. Results will be reported as an odds ratios (OR), 95% CI and exact *P*-values.

A covariate adjusted analysis of the effect of treatment on the primary outcome will be undertaken. All prognostic variables and stratification variables at randomisation (ulcer area and NPUAP grade) will be eligible for inclusion in the covariate adjusted model. Prognostic variables shown to be strongly associated with outcome, even if not shown to be imbalanced between treatment groups, will be screened for inclusion in the covariate adjusted model as they may remove bias from the estimate of treatment effect.

Univariate logistic regression will be conducted to evaluate the relationship between each prognostic variable identified and the study primary outcome. Prognostic variables (and those with a strong imbalance at baseline) with a Likelihood Ratio Test (LRT) *P*-value less than or equal to 0.15 will qualify for evaluation in the maximum covariate adjusted model. Inferences will not be drawn from the interpretation of this univariate *P*-value, but will simply be used to describe the strength of association between the prognostic variable and the primary outcome.

All identified variables will be included in a maximum covariate adjusted logistical regression model. The treatment group term will be forced to stay in the maximum model; the model outcome will be the primary outcome. Using a backwards-stepwise elimination from the maximum model, the final covariate adjusted model will contain all prognostics and unbalanced variables known to have a meaningful bias on the estimate of the treatment effect. The LRT *P*-value for the estimate of treatment effect from this model will be reported, together will the covariate adjusted OR for treatment effect, and the appropriate 95% CI.

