#### Primary endpoint

The primary endpoint will be percentage of all ulcers healed at or before 24 weeks (6 months). Healing will be defined as epithelialisation maintained for 4 weeks and will be confirmed by an observer blind to the randomisation group.

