#### Duration of participant involvement

If the ulcer remains unhealed, participants will have fortnightly assessments by the researcher and will remain in the study for 24 weeks. If the ulcer heals, they will have two more fortnightly assessments. If the ulcer remains healed, they will then have only their 12-week and 24-week assessments, unless these have already been done. If the ulcer heals at 22 or 24 weeks, the participant will have two further fortnightly assessments to confirm healing.

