#### Secondary outcomes

Testing of the secondary outcome variables is exploratory and the results should mainly be used for exploratory purposes. On this basis, no adjustments for multiple testing will be performed.

The time to complete healing of the reference ulcer between the two randomized groups is an important secondary outcome and will be compared using survival analysis. Kaplan-Meier survival curves will be produced for the 2 groups and the median time to healing with 95% CI presented. Treatment effect will be explored using a Cox proportional hazards model including stratification factors (ulcer size and grade) initially. Participants’ heel ulcers that are not healed will be treated as censored and their date of trial exit, or date of last available assessment, or 168-day/trial cessation, as appropriate, will be used to calculate their duration in the trial. Hazard ratio with 95% CI will be given.

Final ulcer area will be analysed by treatment group for those who remain unhealed at the end of the study, using linear regression. As this exploratory analysis will include a subset of the participants, the analysis will be adjusting for baseline area, and any other variables that are found to be imbalanced at baseline (ANCOVA: on both an ITT and PP basis).

Ulcer related pain (measured on a VAS), will be analysed using linear regression and adjusting for baseline pain score, ulcer area, duration of ulcer, and ulcer type on both an ITT and PP basis.

Scores on standardised scales (EQ-5D) will be calculated in line with the guidelines provided by the original authors. The three domain scores will be calculated on the CWIS for each participant, in line with the standard instructions for use: descriptive statistics will be used to summarise these at each assessment. The standardised areas under the curve (area under the curve for each participant adjusted for the duration of available data) will be reported for both groups and compared using a Wilcoxon rank sum test.

*Secondary variables: Descriptive*

All other variables that will not be modelled formally will be considered descriptively. These are:(i)*Concomitant medications*

All concomitant medications will be listed descriptively by study treatment.(ii)Usual wound assessment and care requirements

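### Confirmed healing counts whenever it occurs, but leaving before it means exclusion from the no-imputation analysis, so the healed percentages are overstated even when loss is random

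*Protocol article*

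**What the plan says.** The Primary endpoint section defines the endpoint as the "percentage of all ulcers healed at or before 24 weeks (6 months"), and healing requires 4 weeks of maintained, blind-confirmed epithelialisation.

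The scoring rules then treat the two outcomes differently:

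- **Healed is final at any visit.** Under Primary outcome, those confirmed healed "but do not attend for the 24-week assessment will be counted as" healed. The Statistical analysis section adds: "Such participants will be deemed to have completed their participation in the efficacy part of the study".
- **Not healed takes the full period.** Duration of participant involvement states: "If the ulcer remains unhealed, participants will have fortnightly assessments by the researcher and will remain in the study for 24 weeks". The only early route to a not-healed score is amputation of the target limb. No rule is given for withdrawal, loss or death before confirmed healing.
- **Missing outcomes.** If 20 to 25% are missing, "then ITT will be completed without imputation in the first instance and repeated with multiple imputation as a sensitivity analysis".

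The Withdrawals section ends participation for repeated missed visits only up to confirmed healing. The sample size section counts 186 completers per group and inflates for dropout.

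**The concern.** A confirmed healer cannot be missing, whereas a participant not yet confirmed healed can be. With no imputation, the healed fraction is confirmed healers divided by confirmed healers plus those unhealed and still followed at week 24 (plus amputations). Losses shrink the second group more than the first, because an unhealed participant is exposed to loss for all 24 weeks and a healer only until confirmation. The result is not a percentage of all ulcers, and loss unrelated to the ulcer is enough to distort it.

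Two things are at stake. The absolute healing percentages would be too high in both arms, and percentage healed is also a listed outcome of the economic model. If the arms lose different numbers, the comparison would tilt towards the arm that loses more. Participants and carers are not blinded, so unequal loss cannot be ruled out.

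**Working it through.** **1. The plan's own figure.** With 40% v 55%, two-sided 5% and 80% power, n = [1.96√(2 × 0.475 × 0.525) + 0.8416√(0.24 + 0.2475)]² / 0.15² = 173 per arm. Continuity correction gives 186. Then 372/0.70 = 531 and 372/0.75 = 496. The stated figures reproduce, and they count completers, which fits an analysis of known outcomes only.

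**2. Inputs.** From the protocol: healing p of 40% and 55%, fortnightly visits, 4-week confirmation, and 509 recruited, so about 254 per arm. Assumed: constant hazards, loss independent of healing, no deaths or amputations. L is the chance of leaving by week 24 for someone whose ulcer does not heal; its values are assumptions.

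**3. Formula** (continuous time, 24 weeks as one unit):

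- λh = −ln(1 − p), λd = −ln(1 − L)
- confirmed healed: H = λh/(λh + λd) × [1 − exp(−(λh + λd))] × exp(−λd × 4/24)
- unhealed and followed: U = (1 − p)(1 − L)
- percentage analysed = H/(H + U); missing = 1 − H − U

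| p | L | H | U | Missing | Analysed % |
|---|---|---|---|---|---|
| 0.40 | 0.30 | 0.322 | 0.420 | 25.8% | 43.4% |
| 0.55 | 0.30 | 0.446 | 0.315 | 23.9% | 58.6% |
| 0.40 | 0.20 | 0.349 | 0.480 | 17.1% | 42.1% |
| 0.40 | 0.35 | 0.308 | 0.390 | 30.2% | 44.1% |
| 0.55 | 0.20 | 0.482 | 0.360 | 15.8% | 57.2% |

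**4. Equal loss of 30%.** The formula gives 43.4% v 58.6%; simulation with fortnightly visits gives 43.0% v 58.3%. The odds ratio is (0.586/0.414)/(0.434/0.566) = 1.85 against the true (0.55/0.45)/(0.40/0.60) = 1.83. The percentages move and the comparison hardly does. Average missingness is (25.8 + 23.9)/2 = 24.9%, inside the protocol's 20 to 25% band. If healing comes later, the inflation is smaller: with 25% missing overall, 42.3% v 57.5% (Weibull shape 1.5) and 41.2% v 56.4% (shape 2.5).

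**5. No effect, loss 20% v 35%.** The formula gives 42.1% v 44.1%, and simulation 41.8% v 43.6%, a false 1.8 points. The numbers analysed are 254 × 0.829 = 210.5 and 254 × 0.698 = 177.3, so SE = √[0.43 × 0.57 × (1/210.5 + 1/177.3)] = 5.05 points. The shift is 1.8/5.05 = 0.356 SE, and the type I error is Φ(−1.604) + Φ(−2.316) = 6.5%; simulation gives 6.4%. With later healing (shape 1.5) the gap is 1.3 points, and 1.3/5.05 = 0.257 gives 5.8%.

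**6. True 40% v 55%, loss 35% control and 20% cast.** The formula gives 57.2 − 44.1 = 13.1 points; simulation gives 13.4. With 177.3 and 213.9 analysed, SE = √(0.441 × 0.559/177.3 + 0.572 × 0.428/213.9) = 5.03 points, so power = Φ(13.1/5.03 − 1.96) = 74%. An undistorted 15 points with the same SE would have Φ(15/5.03 − 1.96) = 85%.

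**7. Does keeping the lost at risk remove it?** This was simulated under no effect, with 40% healing, 250 per arm and 4-week confirmation. At 15% v 30% missing, a 24-week Kaplan-Meier comparison gives 0.0 points and 5.2% error, against 2.3 points and 7.5% without imputation. At 20% v 30% it gives 0.1 points and 5.6%, against 1.7 points and 6.8%. These runs contain no deaths or amputations.

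**8. Does scoring the lost as not healed remove it?** No, the bias reverses. In step 5 the arms would show H alone, 34.9% v 30.8%, or 4.1 points against the arm with more loss.

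**The case against.** The strongest reply is that exclusion of the lost is inferred. The rule set is introduced as what classification will include, the ITT population is everyone randomised, the no-imputation wording covers only 20 to 25% missing, and an analysis plan not shown may classify withdrawals and deaths. This stands in part. But scoring the lost as not healed would itself be an imputation, so exclusion is the natural reading, and the completer-based sample size agrees with it.

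Second, the effect on the comparison needs unequal loss. The protocol gives only overall attrition of 25 to 30%. This stands: the unequal-loss figures illustrate and do not predict.

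Several stronger readings are tempting but unsupported:

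- *Everyone lost was unhealed when last seen.* Someone may epithelialise and leave inside the 4-week window. The correct term is not confirmed healed, and the window weakens the bias. Leaving it out of the simulation gives 2.7 points and 8.1% in place of 1.8 and 6.4%.
- *The time-to-healing analysis is already the correct version.* Under Secondary outcomes, "heel ulcers that are not healed will be treated as censored". As written, that censors amputation, which the primary rules score as not healed, and it does not deal separately with death. It also promises curves, medians and a hazard ratio, not a rival 24-week percentage.
- *The multiple imputation uses baseline covariates only.* Its model is not specified.
- *The true percentages could be 28% v 38.5%* (0.40 × 186/265.7 and 0.55 × 186/265.7). That assumes nobody lost would heal. It contradicts random loss and would apply to any complete-case analysis.
- *The inflated figure is the economic model's input.* The protocol lists percentage healed as a model outcome without saying which estimate is used.

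**Conclusion.** The point holds, with modest size. Read naturally, the scoring rules and the no-imputation analysis give a healed percentage selected on outcome. At equal 30% loss it is about 3 points too high in each arm, less if healing comes late. With equal loss hazards the odds ratio is essentially unaffected. Under the assumed 20% v 35% imbalance, the false difference is about 1 to 2 points with type I error of about 6%. Reversed against a true effect, the same imbalance costs about 2 points of the 15 and leaves power of about 74%. All of this rests on the assumed healing shape, independent loss and the absence of deaths and amputations. It justifies a supporting estimate and clearer rules, not replacement of the primary analysis.

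**What to change.** In Statistical analysis, Primary outcome and Missing data:

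- Whatever the level of missingness, report beside the logistic regression the 24-week confirmed-healing percentage per arm, and the difference with 95% CI, from a cumulative incidence curve. Count losses at risk until their last ulcer assessment. Treat amputation and death as competing events, not as censoring.
- State how withdrawal, loss and death before confirmed healing are classified in the logistic regression.
- Have any multiple imputation include the week last seen not healed and the last ulcer area.
- Show the analysis scoring all lost participants as not healed only as a bound.
- Use the corrected percentages wherever percentage healed enters the cost-effectiveness model.

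The fortnightly ulcer data are already collected, so the cost is wording, some programming and slightly lower reported healing percentages.

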## Methods/Design

### Study configuration

This will be an observer-blind, randomised controlled trial. Randomisation will be stratified by ulcer grade (National Pressure Ulcer Advisory Panel-European Pressure Ulcer Advisory Panel (NPUAP-EPUAP) Grade 2, 3 or 4, see below) and by ulcer area (greater than or equal to 25 mm^2^ and less than or equal to 1 cm^2^ or greater than 1 cm^2^), using random permuted blocks of randomly varying size. Randomisation will be undertaken by Nottingham Clinical Trials Unit (CTU), using a web-based system.

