Routine data related to the formal assessment of the wound and surrounding skin will be presented descriptively with counts and rates; provision of off-loading will be presented as categorical data with changes to device requirements recorded throughout the intervention period noted.

*Secondary variables: Safety*

ADEs and withdrawals comprise safety data and will be presented in line with standard reporting requirements. SADEs will also be considered and presented by group. Secondary outcome measures (incidence of foot infection, major amputation, minor amputation, revascularisation and falls leading to hospital admission) will be reported.

Using a negative binomial model and adjusting for the same covariates as the primary analyses, the numbers of adverse events in each participant between treatment groups will be compared.

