#### Determination of sample size

The expected prevalence of healed ulcer in the control group and the treatment group is 40% and 55%, respectively, at 24 weeks. With α = 0.05 and β = 1-power (power 80%) and an estimated rate of dropouts of 30% a total of 531 patients of both genders will be included (to achieve 186 in each group completing the intervention phase). With 25% attrition, the number required is 496 (to achieve 186 in each group). The study will aim to recruit 500 patients and closely monitor the number of cases where the primary outcome data are missing. All secondary analyses will be interpreted with caution as the sample size calculation is based on the primary outcomes only. Internet-based treatment assignment will be determined by a computer-generated pseudo-random code using random permuted blocks of randomly varying size, created by the Nottingham CTU. Trial participants will be allocated with equal probability to each treatment arm with stratification by ulcer grade and ulcer size.

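### No single primary model is fixed: the unadjusted logistic analysis leaves out the stratification factors, and the adjusted one selects covariates from the outcome data without forcing those factors in

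*Protocol article*

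**What the plan says.** Allocation is 1:1 in permuted blocks, stratified by ulcer grade (2, 3 or 4) and by ulcer area in two classes, so there are six strata (Study configuration; Randomisation and blinding; Determination of sample size).

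Under Primary outcome the article sets out two analyses of confirmed healing:

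- First, "the unadjusted analysis of the effect of treatment on the primary outcome will be assessed using Logistic Regression", reported as an odds ratio (OR) with 95% CI and P-value.
- Then a covariate-adjusted logistic model. Prognostic variables and the two stratification variables "will be eligible for inclusion in the covariate adjusted model". Candidates qualify on a univariate likelihood ratio P-value of 0.15 or less and then go through backward elimination. The only protected term is treatment: "The treatment group term will be forced to stay in the maximum model". The final model is to hold the variables regarded as biasing the treatment estimate to a meaningful extent; no numerical criterion is given. This model yields a second OR, CI and P-value.

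Under Secondary outcomes, the Cox model for time to healing includes ulcer size and grade from the start. The comparison of adverse-event counts is to be made "adjusting for the same covariates as the primary analyses".

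**The concern.** Three features of the text sit badly together.

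1. The design balances the arms on grade and area, but the first analysis ignores both. If they are prognostic, the model-based standard error overstates the sampling variation of the unadjusted estimate, so the test is somewhat conservative.
2. The adjusted model is not fixed in advance. Its covariates depend on the trial's outcomes, the design factors can be lost, and retention is tied to movement of the treatment estimate. For an odds ratio such movement is not evidence of bias: adding a prognostic factor moves the OR away from 1 even when the factor is perfectly balanced (non-collapsibility).
3. Two results for one endpoint are reported without a ranking. One estimates a marginal OR and the other a conditional OR, so they answer slightly different questions and can fall on opposite sides of 0.05.

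**Working it through.** **The plan's own figure.** Inputs from Determination of sample size: the planned healing rates ("The expected prevalence of healed ulcer in the control group and the treatment group is 40% and 55%, respectively, at 24 weeks"), α 0.05, power 80%. From Statistical analysis: "Two-sided statistical test will be performed".

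- Uncorrected: n = [1.960 × √(2 × 0.475 × 0.525) + 0.842 × √(0.40 × 0.60 + 0.55 × 0.45)]² / 0.15² = 172.8, so 173 per arm.
- With continuity correction: n′ = (172.8/4) × [1 + √(1 + 4/(172.8 × 0.15))]² = 185.9, so 186 per arm, as stated.
- Totals: 372/0.70 = 531.4 (stated 531) and 372/0.75 = 496 (stated 496).

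The sample size reproduces, and nothing below alters it.

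**Simulation.** 3,000 trials per scenario, 186 per arm, permuted blocks in six strata, healing 40% v 55% (or 40% in both arms under the null). Three analyses were compared: unadjusted; grade and area forced in; and the plan's selection.

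Assumptions not in the article:

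- Area split 50/50; grades 40/40/20%.
- Area OR 0.67 / 0.50 / 0.33 and OR per grade step 0.77 / 0.67 / 0.50 (weak / moderate / strong).
- Six further candidate covariates, three of them prognostic (OR per SD 1.25 / 1.35 / 1.50).
- Every candidate, including grade and area, faces the 0.15 screen; removal at P > 0.05.

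| | Weak | Moderate | Strong |
|---|---|---|---|
| Type I error, unadjusted | 4.6% | 4.5% | 4.0% |
| Type I error, strata forced in | 4.9% | 5.0% | 5.3% |
| Type I error, selected model | 5.2% | 5.3% | 5.2% |
| Type I error if either P (unadjusted or selected) counts | 5.7% | 6.1% | 6.2% |
| Power, unadjusted | 84.2% | 83.7% | 85.0% |
| Power, strata forced in | 84.3% | 83.9% | 86.7% |
| Unadjusted and selected on opposite sides of 0.05, null | 1.7% | 2.4% | 3.2% |
| Same, design effect | 3.2% | 5.4% | 6.3% |
| Area kept by selection, null | 47% | 88% | 100% |
| Grade kept by selection, null | 35% | 67% | 98% |
| Mean SE of log OR, unadjusted, null | 0.212 | 0.212 | 0.212 |
| Sampling SD of log OR, unadjusted, null | 0.211 | 0.210 | 0.202 |
| Mean SE of log OR, strata forced in, null | 0.215 | 0.218 | 0.225 |
| Mean log OR, unadjusted, design effect | 0.614 | 0.608 | 0.613 |
| Mean log OR, strata forced in, design effect | 0.631 | 0.642 | 0.687 |

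Monte Carlo error at 5% is √(0.05 × 0.95/3000) = 0.4 points; at 84% it is √(0.84 × 0.16/3000) = 0.7 points. Only the 4.0% is clearly below 5%.

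**Cross-check on size.** In the strong case, 1.96 × 0.212/0.202 = 2.06, a two-sided tail of about 4.0%, which agrees with the table.

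**Non-collapsibility.** The design's marginal log OR is ln(0.55/0.45) − ln(0.40/0.60) = 0.606. The unadjusted mean stays close to this (0.613 in the strong case). With the balanced strata forced in, the mean moves to 0.687, that is, from an OR of e^0.613 = 1.85 to e^0.687 = 1.99. Neither is biased; they are different quantities. A retention rule that reads this shift as bias misreads it.

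**Text against text.** An unadjusted primary analysis has no covariates, so the safety wording about covariates of the primary analyses fits only the adjusted model. The Cox model starts with the stratification factors; the logistic analysis of the primary outcome does not.

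**The case against.** - **The SAP may rank the analyses.** The unadjusted model is listed first, and the sample size rests on two unadjusted proportions, so a reader could take it as primary. A separate plan may say so. This stands in part: the missing ranking alone would be no finding in a condensed article. But the article does state a selection procedure, and its safety wording points to the other model. A SAP that follows the article inherits both.
- **The text need not mean that grade and area face the 0.15 screen.** It lists prognostic and stratification variables separately, and the screen names prognostic and imbalanced variables. This stands: the retention percentages above rest on the stricter reading. On either reading, only treatment is protected from elimination.
- **The selected model has more power** (84.6% / 85.8% / 89.7%), and its own size is within simulation error of 5%. True, but the gain comes from adjusting for prognostic covariates, and these can be listed in advance.
- **A reader might infer that the unadjusted CI is too wide and that adjustment would narrow it.** The article does not support this. The excess of the SE over the sampling SD is about 0% to 5% (0.212/0.211 to 0.212/0.202) and clear only with strong strata. Forcing the factors in raises the SE of the log OR, from 0.212 to between 0.215 and 0.225.
- **A reader might put the false-positive rate at 7% to 8%.** That takes 12 candidate covariates (7.1% to 7.9% in 1,500 simulated trials per scenario), removal at P > 0.05, and a rule that either P-value is enough. The article gives no candidate count, no removal threshold and no such rule.

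**Conclusion.** The point holds in a moderate form and should be fixed; it does not undermine the trial. The text establishes that the unadjusted analysis omits the design factors, that the adjusted model is built from the outcome data with only treatment protected, and that two results are reported in an article whose own sections disagree on which is primary.

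The numerical consequences are small and depend on assumed prognostic strength: a slightly conservative unadjusted test (size 4.0% to 4.6%), 0.1 to 1.7 points of power forgone, and design factors that can drop out by chance when they are weakly or moderately prognostic. A type I error of about 6% arises only if either P-value were accepted, with six further candidates and removal at P > 0.05 assumed. The stronger reason to act is that the model and the deciding result should be known before the data are seen.

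**What to change.** Before unblinding:

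1. Name one primary analysis: logistic regression of confirmed healing on treatment, with grade and baseline area forced in, in line with the article's Cox model.
2. Label the unadjusted OR and any further-adjusted model as sensitivity analyses. Replace the 0.15 screen, backward elimination and retention by effect on the treatment estimate with a covariate list fixed in advance.
3. Reword the adverse-event analysis so that its covariates are those of the named primary model.

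A minor editorial point: if area enters as the randomisation stratum, use one boundary. The Abstract puts an ulcer of exactly 1 cm² in the upper class; Study configuration ("less than or equal to 1 cm^2^ or greater than 1 cm^2") puts it in the lower.

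The cost is a change of wording. Grade and traced area are recorded at the randomisation visit, so no new data are needed, and the required sample size stays the same.
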